## 9. STATISTICAL METHODOLOGY

### 9.1 General

Data listings will be provided for all data that is databased. Summary statistics and statistical analysis will only be presented for data where detailed in this SAP. For continuous data, summary statistics will include the arithmetic mean, arithmetic standard deviation (SD), median, min, max and N; for log-normal data (e.g. the PK parameters: Area under the concentration

versus time curve [AUCs] and maximum observed drug concentration [ $C_{max}$ ]) the geometric mean and geometric coefficient of variation (CV%) will also be presented. For categorical data, frequency count and percentages will be presented. Data listings will be provided for all subjects up to the point of withdrawal, with any subjects excluded from the relevant population highlighted. Summary statistics and statistical analyses will generally only be performed for subjects included in the relevant analysis population. For the calculation of summary statistics and statistical analysis, unrounded data will be used.

Mean change from baseline is the mean of all individual subjects' change from baseline values. Each individual change from baseline will be calculated by subtracting the individual subject's baseline value from the value at the timepoint. The individual subject's change from baseline values will be used to calculate the mean change from baseline using a SAS procedure such as Proc Univariate.

Data analysis will be performed using SAS® Version 9.4 or greater.

## **9.2 Demographics and Subject Disposition**

Subject disposition will be listed. The demographic variables age, sex, race, ethnicity, country of enrolment, body weight, height and body mass index will be summarized by treatment, and listed. Screening triglyceride (TG) and low-density lipoprotein cholesterol (LDL-C) will also be summarized by treatment, and listed. All other demographic variables will be listed only.

A disposition for all enrolled subjects will also be provided.

## **9.3 Pharmacokinetic Assessment**

### **9.3.1 Pharmacokinetic Analysis**

The PK parameter estimates will be determined using non-compartmental procedures in validated software program (Phoenix WinNonlin Version 8.1 or later).

Plasma concentrations of LY3475766 will be used to determine the following PK parameters, when possible:

| Parameter                                                                  | Units   | Definition                                                                                                                              |
|----------------------------------------------------------------------------|---------|-----------------------------------------------------------------------------------------------------------------------------------------|
| AUC(0-t last )                                                  | h*µg/mL | area under the concentration versus time curve from time zero to time t, where t is the last time point with a measurable concentration |
| AUC(0-∞)                                                                   | h*µg/mL | area under the concentration versus time curve from time zero to infinity                                                               |
| %AUC(t last -∞)                                                 | %       | percentage of AUC(0-∞) extrapolated                                                                                                     |
| C max                                                           | µg/mL   | maximum observed drug concentration                                                                                                     |
| t max                                                           | h       | time of maximum observed drug concentration                                                                                             |
| t 1/2                                                           | h       | half-life associated with the terminal rate constant (λ z ) in non-compartmental analysis                                    |
| CL                                                                         | L/h     | total body clearance of drug calculated after IV administration                                                                         |
| CL/F                                                                       | L/h     | apparent total body clearance of drug calculated after extra-vascular administration                                                    |
| V z                                                             | L       | volume of distribution during the terminal phase after IV administration                                                                |
| V z /F                                                          | L       | apparent volume of distribution during the terminal phase after extra-vascular administration                                           |
| F                                                                          | %       | bioavailability based on AUC(0-∞)                                                                                                       |
| $F = \frac{AUC [SC] \times Dose[IV]}{AUC [IV] \times Dose[SC]} \times 100$ |         |                                                                                                                                         |

Additional PK parameters may be calculated, as appropriate.

The software and version used for the final analyses will be specified in the CSR. Any exceptions or special handling of data will be clearly documented within the final study report.

Formatting of tables, figures and abbreviations will follow the Eli Lilly Global PK/PD/TS Tool: NON-COMPARTMENTAL PHARMACOKINETIC STYLE GUIDE. The version of the tool effective at the time of PK analysis will be followed.

### General PK Parameter Rules

- Actual sampling times will be used in the final analyses of individual PK parameters, except for non-bolus pre-dose sampling times which will be set to zero. For non-bolus, multiple dose profiles, the pre-dose time will be set to zero unless a time deviation falls outside of the protocol blood collection time window which is considered to impact PK parameter derivation.
- Cmax and tmax will be reported from observed values. If Cmax occurs at more than one time point, tmax will be assigned to the first occurrence of Cmax.
- AUC parameters will be calculated using a combination of the linear and logarithmic trapezoidal methods (linear-log trapezoidal rule). The linear trapezoidal method will be

applied up to  $t_{\max}$  and then the logarithmic trapezoidal method will be used after  $t_{\max}$ . The minimum requirement for the calculation of AUC will be the inclusion of at least three consecutive concentrations above the lower limit of quantification (LLOQ), with at least one of these concentrations following  $C_{\max}$ .

- AUC(0- $\infty$ ) values where the percentage of the total area extrapolated is more than 20% will be flagged. Any AUC(0- $\infty$ ) value excluded from summary statistics will be noted in the footnote of the summary table.
- Half-life ( $t_{1/2}$ ) will be calculated, when appropriate, based on the apparent terminal log-linear portion of the concentration-time curve. The start of the terminal elimination phase for each subject will be defined by visual inspection and generally will be the first point at which there is no systematic deviation from the log-linear decline in plasma concentrations. Half-life will only be calculated when a reliable estimate for this parameter can be obtained comprising of at least 3 data points. If  $t_{1/2}$  is estimated over a time window of less than 2 half-lives, the values will be flagged in the data listings. Any  $t_{1/2}$  value excluded from summary statistics will be documented in the footnote of the summary table.
- A uniform weighting scheme will be used in the regression analysis of the terminal log-linear portion of the concentration-time curve.
- The parameters based on the predicted last observed concentration will be reported.

### Individual PK Parameter Rules

- Only quantifiable concentrations will be used to calculate PK parameters with the exception of special handling of certain concentrations reported below the lower limit of quantitation (BQL). Plasma concentrations reported as BQL will be set to a value of zero when all of the following conditions are met:
  - The compound is non-endogenous.
  - The samples are from the initial dose period for a subject or from a subsequent dose period following a suitable wash-out period.
  - The time points occur before the first quantifiable concentration.
- All other BQL concentrations that do not meet the above criteria will be set to missing.
- Also, where two or more consecutive concentrations are BQL towards the end of a profile, the profile will be deemed to have terminated and therefore any further quantifiable concentrations will be set to missing for the calculation of the PK parameters unless it is considered to be a true characteristic of the profile of the drug.
- For multiple-dosing data, when pre-dose concentrations are missing, the value to be substituted will be minimum observed concentration for the dosing interval.

---

### **Individual Concentration vs. Time Profiles**

- Individual concentrations will be plotted utilizing actual sampling times.
- The terminal point selections will be indicated on a semi-logarithmic plot.

### **Average Concentration vs. Time Profiles**

- The average concentration profiles will be graphed using scheduled (nominal) sampling times.
- The average concentration profiles will be graphed using arithmetic average concentrations.
- The pre-dose average concentration for single-dose data from non-endogenous compounds will be set to zero. Otherwise, only quantifiable concentrations will be used to calculate average concentrations.
- Concentrations at a sampling time exceeding the sampling time window specified in the protocol, or  $\pm 10\%$ , will be excluded from the average concentration profiles.
- Concentrations excluded from the mean calculation will be documented in the final study report.
- A concentration average will be plotted for a given sampling time only if 2/3 of the individual data at the time point have quantifiable measurements that are within the sampling time window specified in the protocol or  $\pm 10\%$ . An average concentration estimated with less than 2/3 but more than 3 data points may be displayed on the mean concentration plot if determined to be appropriate and will be documented within the final study report.

### **Treatment of Outliers during Pharmacokinetic Analysis**

Application of this procedure to all PK analyses is not a requirement. Rather, this procedure provides justification for exclusion of data when scientifically appropriate. This procedure describes the methodology for identifying an individual value as an outlier for potential exclusion, but does not require that the value be excluded from analysis. The following methodology will not be used to exclude complete profiles from analysis.

#### Data within an Individual Profile

A value within an individual profile may be excluded from analysis if any of the following criteria are met:

- For PK profiles during single dosing of non-endogenous compounds, the concentration in a pre-dose sample is quantifiable.

- For any questionable datum that does not satisfy the above criteria, the profile will be evaluated and results reported with and without the suspected datum.

#### Data between Individual Profiles

1. If  $n < 6$ , then the dataset is too small to conduct a reliable range test. Data will be analyzed with and without the atypical value, and both sets of results will be reported.
2. If  $n \geq 6$ , then an objective outlier test will be used to compare the atypical value to other values included in that calculation:
  - a. Transform all values in the calculation to the logarithmic domain.
  - b. Find the most extreme value from the arithmetic mean of the log transformed values and exclude that value from the dataset.
  - c. Calculate the lower and upper bounds of the range defined by the arithmetic mean  $\pm 3 \times \text{SD}$  of the remaining log-transformed values.
  - d. If the extreme value is within the range of arithmetic mean  $\pm 3 \times \text{SD}$ , then it is not an outlier and will be retained in the dataset.
  - e. If the extreme value is outside the range of arithmetic mean  $\pm 3 \times \text{SD}$ , then it is an outlier and will be excluded from analysis.

If the remaining dataset contains another atypical datum suspected to be an outlier and  $n \geq 6$  following the exclusion, then repeat step 2 above. This evaluation may be repeated as many times as necessary, excluding only one suspected outlier in each iteration, until all data remaining in the dataset fall within the range of arithmetic mean  $\pm 3 \times \text{SD}$  of the log-transformed values.

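### If run on every dose group, the 3 SD between-profile PK outlier rule would flag a valid value in about 31% of clean six-subject groups, and the SAP is unclear on whether flagged values must go

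*Combined protocol and SAP*

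**What the plan says.** The rule is in SAP Section 9.3.1, under Data between Individual Profiles. For n ≥ 6 the steps are:

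- 2a: "Transform all values in the calculation to the logarithmic domain".
- 2b: "Find the most extreme value from the arithmetic mean of the log transformed values and exclude that value from the dataset".
- 2c: "Calculate the lower and upper bounds of the range defined by the arithmetic mean" ± 3 SD "of the remaining log-transformed values".
- 2d and 2e: a value inside the range is kept. If it is outside, "then it is an outlier and will be excluded from analysis".

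The test may be repeated, removing one value at a time, while at least six values remain. For n < 6 the SAP regards a range test as unreliable and has the results reported both with and without the questioned value. It sets no such requirement for n ≥ 6. There, the paragraph on reporting excluded values asks only that they be documented in the final report.

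The introduction to the procedure (Treatment of Outliers during Pharmacokinetic Analysis) is softer: "Application of this procedure to all PK analyses is not a requirement". It presents the method as a way to identify candidates for exclusion that "does not require that the value be excluded from analysis". It also rules out using the method to drop whole profiles.

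**The concern.** A 3 SD limit looks strict, because for one pre-chosen value and a known SD it would be crossed about 0.3% of the time. Neither condition holds here. The tested value is chosen because it is the most extreme, and at n = 6 the SD comes from five values and has 4 degrees of freedom. The SAP calls the test objective at n = 6 and the dataset too small at n = 5, although little changes between the two.

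The values at risk feed the geometric means and CV% by dose, the power model for dose proportionality, and the between-subject variability that Section 9.3.2 promises. Removing valid extremes makes variability look smaller than it is. Protocol Section 5.4 says the PK data will help identify the dose range for later studies.

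**Working it through.** The documents state no error rate for the rule, so there is no planned figure to reproduce.

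**Group size.** SAP Section 7 gives 36 evaluable subjects on LY3475766 and 12 on placebo, and Section 5 gives six cohorts. Then 36/6 = 6 active subjects per dose, which agrees with the 3:1 allocation (36:12). Equal cohorts are assumed. The 300 mg cohort is repeated (Protocol Appendix 6), so that group could reach about 12 if both runs are combined.

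**Flag rate for one group and one parameter.** For values normal on the log scale, (value − mean of the others) / (SD of the others × √(1 + 1/(n−1))) follows a t distribution with n − 2 degrees of freedom. A 3 SD limit is therefore a limit of 3/√(1 + 1/(n−1)) on the t scale.

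| n | t limit | P per value | n × P |
|---|---|---|---|
| 6 | 3/√1.2 = 2.739 | 0.0520 | 0.312 |
| 7 | 2.777 | 0.0390 | 0.273 |
| 12 | 2.872 | 0.0166 | 0.199 |

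At n = 6 the product is exact. Expressed as a distance from the full-group mean in full-group SDs, the limit is 1.648. Two of six values cannot both exceed √(5/2) = 1.581. Simulating steps 2a to 2e on 1,000,000 clean groups gave 31.2% at n = 6, 27.3% at n = 7 and 19.9% at n = 12. With heavier tails on the log scale (t with 5 df) the rate at n = 6 was 38.7%.

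**Across six dose groups of six, if every group is tested.** The expected number of flagged groups per parameter is 6 × 0.312 = 1.87. The chance of at least one is 1 − (1 − 0.312)^6 = 0.89. With the 300 mg group at n = 12 it is 1 − 0.688^5 × 0.801 = 0.88.

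**Effect on variability at n = 6, if every flag is acted on** (simulated, true log-SD = 1):

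- Mean log-SD falls from 0.951 to 0.813, a ratio of 0.855, so about 15% lower.
- Mean log-variance falls from 1.00 to 0.78, so 22% lower.
- Within flagged groups the mean log-SD falls from 0.951 to 0.507, which is 53% of its full-data value.
- Taking a true CV of 30% as an illustration, the average variance corresponds to a CV of about 26%.

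**Effect on the power model.** This is where the PK section plans its confidence intervals. The six planned doses were simulated with six log-normal values each, with exclusion automatic in every group. Mean residual variance fell from 1.00 to 0.85. Coverage of the nominal 90% interval for the slope fell from 90% to 84%. The slope itself was not biased.

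**Multiplier for a 5% flag rate per group and parameter.** k = t(upper tail 0.05/(2n), n−2 df) × √(1 + 1/(n−1)). At n = 6, 4.851 × 1.0954 = 5.31. At n = 12, 3.691 × 1.0445 = 3.86.

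**The case against.** The strongest objection is that the procedure is optional. Its introduction makes both its use and the exclusion a matter of scientific judgement, and the n ≥ 6 rule starts from a value already questioned: "then an objective outlier test will be used to compare the atypical value to other values included in that calculation". It is not written as a routine screen of every group and parameter. This stands. A reader might infer that the trial will discard a valid value in 31% of groups, or that the chance of losing at least one per parameter is 89%. The documents support neither as a forecast. Each needs every group to be tested and every flag acted on.

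Three further points stand in part:

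- Six per group is inferred. Replacements and the repeated 300 mg cohort may enlarge a group, which lowers the rate. If a parameter is missing for one of six subjects, the both-ways rule for n < 6 applies.
- Exclusions will be visible in the final report and all data will be listed, so a reader could restore a dropped value.
- PK is a secondary objective, the sample size is not powered for a test, and no document says these CVs will set a later sample size.

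Discretion does not remove the problem. Step 2e and the introduction can be read as different instructions, so two analysts following the SAP could report different results. A test that supports removing a valid value in up to 31% of clean groups is weak justification for doing so, and choosing when to run it after seeing the data adds selection. The trigger may filter little, because a value more than 3 SD from its five neighbours is one likely to look atypical. Documenting an exclusion is also less than reporting the full-data result.

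**Conclusion.** The concern holds in conditional form. Under log-normality the rule flags a valid value in 31% of clean groups of six, 27% of seven and 20% of twelve, per PK parameter, if it is run on every group. These are upper limits on the share of clean groups losing a value at the first pass. The actual rate depends on choices the SAP leaves open and cannot be computed from it.

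The variability and coverage figures assume six active subjects in every group, testing in every group and action on every flag. The 22% loss of variance applies to a single group's log-variance. The smaller 15% applies to the residual variance of the power model. A reader might also infer that the dose-proportionality estimate is biased. With log-normal data the removal is symmetric and the slope is not biased; its interval is too narrow.

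As written, step 2e would understate between-subject variability if followed, it conflicts with the procedure's introduction, and the safeguard for n < 6 stops at the group size the trial plans.

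**What to change.** In SAP Section 9.3.1:

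1. Keep all values in the main PK analysis unless a dosing, sampling or assay error is documented.
2. Extend the existing n < 6 provision to every n, so that results are reported with and without any value judged atypical.
3. Reword step 2e to agree with the introduction, so that a value outside the limits is flagged and not automatically removed.
4. If a test is kept as a flag, replace the fixed 3 with a multiplier that depends on n: about 5.3 at n = 6 and 3.9 at n = 12 for a 5% rate per dataset. The 5% is a choice, since the SAP states no target.

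The repeat step cannot operate at n = 6, because one exclusion leaves five values. Deleting it would matter only for larger groups, such as a combined 300 mg group.

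The cost is a few sentences of SAP wording and, occasionally, an extra set of PK summary rows. No new data are needed.

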#### Reporting of Excluded Values

Individual values excluded as outliers will be documented in the final report. Approval of the final report will connote approval of the exclusion.

### **9.3.2 Pharmacokinetic Statistical Methodology**

PK dose proportionality will be assessed using a power model. Log-transformed  $C_{\max}$ ,  $\text{AUC}(0-t_{\text{last}})$  and  $\text{AUC}(0-\infty)$  estimates will be evaluated using a power model (where log-dose acts as an explanatory variable) to estimate ratios of dose-normalized geometric means and corresponding 90% confidence intervals (CIs).

The estimated ratio of dose-normalized geometric means of PK parameters between the highest and lowest doses will be used to assess dose proportionality. Between subject variability estimates will also be provided.

Example SAS code for the analysis:

```
proc mixed data=xxx;  
model log_pk = log_dose / alpha=0.1 cl solution outpred=resids ddfm=kr;  
estimate 'xx mg' intercept 1 log_dose yy / alpha=0.1 cl; /*Log value of xx*/  
estimate 'zz mg - xx mg' log_dose pp / alpha=0.1 cl; /*Difference in log  
values of zz and xx*/  
ods output solutionf=est;  
ods output estimates=estims;  
run;
```

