Data to be reviewed prior to dose-escalation decisions, including the timing and scope of these reviews, are described in Section 7.4.1. The escalation of doses is based on the area under the concentration versus time curve (AUC) exposures to maintain approximately 3-fold between each escalating dose level except at the highest dose where the increment will be lower than 3-fold. The bioavailability (F) of an SC-administered monoclonal antibody is generally between 50% and 80%; thus, 100 mg and 300 mg SC are expected to be equivalent to 50 mg to 80 mg IV, and 150 mg to 240 mg IV in AUC, respectively.

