## 5.5. Justification for Dose

Doses of 10, 30, and 1000 mg IV and 100, 300, and 600 mg SC LY3475766 were selected based on preclinical pharmacology and toxicology data.

The doses planned for this study were selected based on nonclinical toxicology studies ([Table GZEA.3](#)) and analysis of preclinical PK/PD data, with the objective of providing acceptable safety margins while allowing the identification of potentially efficacious dose levels. Preclinical PK and PK/PD data from a mouse model of elevated TG levels (cholesteryl ester transfer protein/apolipoprotein [apo] A1 double transgenic) were used to estimate a minimal anticipated biological effect level (MABEL) dose of 0.3 mg/kg IV in humans. This dose level is projected to produce less than a 10% reduction in TG at the nadir following a single dose.

LY3475766 is a humanized immunoglobulin (Ig) G4 monoclonal antibody that binds to the ANGPTL3/8 complex and thus is not expected to have any direct interaction with the immune system. Due to the anticipated low risk nature of LY3475766 and its target, it is appropriate to use the starting dose of 10 mg IV (0.14 mg/kg for a 70-kg person) in this study, which is about one-half of the estimated MABEL. The exposures (AUC) at the rat and monkey no-observed-adverse-effect levels (NOAELs) (100 mg/kg and 150 mg/kg, respectively) provide exposure multiples of 520X and 687X, respectively, relative to the projected exposure at the proposed human starting dose ([Table GZEA.2](#)).

The anticipated exposure multiples at the planned maximum human dose of 1000 mg IV (14.3 mg/kg) relative to the nonclinical NOAEL exposures are 5X and 7X for the rat and monkey, respectively ([Table GZEA.2](#)). This maximal dose was chosen to provide a robust exploration of dose response, including durability of response, while maintaining a margin of safety to the toxicology findings.

**Table GZEA.2. Margin of Safety for Intravenous Administration of LY3475766 Based on Administered Dose and Predicted Exposure**

|                                                                                     | Dose
(mg/kg) a | AUC
(µg•h/mL)                             | Dose Multiple b            |                                     | Exposure Multiple b        |                                     |

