#### **10.3.2.2. Pharmacokinetic Statistical Inference**

The descriptive statistics (geometric mean and coefficient of variation) for the PK parameters will be provided for each dose level. Log-transformation will be applied to  $C_{max}$  and AUC in calculation of geometric mean and coefficient of variation.

The dose proportionality for LY3475766 will be assessed for AUC and  $C_{max}$  using a power model. The power parameter will be evaluated to determine the dose proportionality.

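### The dose-proportionality power model has no route term, so SC bioavailability below 100% biases the 1000:10 mg ratio below 1 even when PK is proportional within each route

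*Combined protocol and SAP*

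**What the plan says.** Protocol 5.5 gives the doses and routes: "Doses of 10, 30, and 1000 mg IV and 100, 300, and 600 mg SC LY3475766 were selected". Protocol 5.1 states that "The bioavailability (F) of an SC-administered monoclonal antibody is generally between 50% and 80" per cent, and from this equates 100 mg SC to 50-80 mg IV and 300 mg SC to 150-240 mg IV in AUC.

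Protocol 10.3.2.2 plans a power model for AUC and Cmax and adds: "The power parameter will be evaluated to determine the dose proportionality". It does not mention route. SAP 9.3.2 says the log-transformed parameters "will be evaluated using a power model (where log-dose acts as an explanatory variable) to estimate ratios of dose-normalized geometric means", with 90% CIs. The example code is "model log_pk = log_dose / alpha=0.1 cl solution outpred=resids ddfm=kr", with no CLASS or BY statement and no route variable. The criterion is: "The estimated ratio of dose-normalized geometric means of PK parameters between the highest and lowest doses will be used to assess dose proportionality". No acceptance limits are given. The section also promises between-subject variability estimates.

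The PK population in SAP 8 is not split by route, and SAP 11 declares no changes from the protocol's analyses. SAP 9.3.1 separates CL from CL/F and Vz from Vz/F. It defines F as a dose-normalized SC-to-IV ratio of AUC(0-∞), without naming the IV cohort or cohorts that serve as reference.

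**The concern.** An SC cohort with F below 1 lies below the IV line by ln(F) on the log scale, whatever its dose. A model with log-dose alone has nowhere to put that shift except the slope and the residual.

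The 300 and 600 mg SC doses lie above the mean log-dose and pull the slope down. The 100 mg SC dose lies slightly below the mean and offsets this only a little. The remaining shift inflates the residual variance.

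Three planned results are affected: the slope, the highest-to-lowest ratio that is the stated criterion, and the model's between-subject variability. A difference between routes, which the protocol itself predicts, would appear as less-than-proportional exposure. More subjects per cohort would not remove the bias. According to protocol 5.4, the PK data are meant to help identify a dose range for later studies.

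**Working it through.** **Inputs from the documents.** Doses and routes (protocol 5.1, 5.5); F of 50-80% (protocol 5.1); predicted AUCs (Tables GZEA.2 and GZEA.3); 36 evaluable active subjects in six cohorts (SAP 7).

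**Assumptions.** 36/6 = 6 active subjects per dose; log-normal errors; between-subject CV of 25% or 35%, since the documents give none; PK exactly proportional within each route.

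**1. The plan's own figures.** 100 mg × 0.5 and × 0.8 = 50 and 80 mg; 300 mg × 0.5 and × 0.8 = 150 and 240 mg. Both ranges are reproduced. Predicted AUC per mg:
- IV: 1324.9/10 = 132.49 and 132485.9/1000 = 132.49.
- SC: 9911.0/100 = 99.11 and 29796.7/300 = 99.32.

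The predictions are therefore proportional within each route. The SC/IV quotient is 99.11/132.49 = 0.748 or 99.32/132.49 = 0.750, so F is about 0.75. That holds only if the SC values, which are steady-state AUCs for multiple dosing, are comparable with the single-dose IV AUC(0-∞).

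**2. Slope bias.** The mean of ln(dose) is 4.886. The deviations from it are:
- IV: -2.584 (10 mg), -1.485 (30 mg), +2.022 (1000 mg).
- SC: -0.281 (100 mg), +0.818 (300 mg), +1.511 (600 mg).

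The sum of squares is 15.997 and the SC deviations sum to 2.047 (from unrounded values). The pooled slope is therefore expected to be 1 + ln(F) × 2.047/15.997 = 1 + 0.128 ln(F). The dose-normalized 1000:10 mg ratio is 100^(slope - 1).

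**3. Inflated variance.** The part of the route shift that log-dose cannot absorb has sum of squares 6 × (1.5 - 2.047²/15.997) = 7.43. The expected residual variance is then σ² + ln(F)² × 7.43/34, with σ² = ln(1 + 0.25²) = 0.0606 at a CV of 25%. At F=0.50 this is 0.0606 + 0.480 × 0.2185 = 0.166, and √(e^0.166 - 1) = 0.42.

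**4. Results.** CI coverage comes from simulated trials with t-based 90% intervals; separate runs agree to about one percentage point.

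| F | Slope | 1000:10 ratio (truth 1.00) | CI contains 1, CV 25% | CI contains 1, CV 35% | Reported CV (truth 25%) |
|---|---|---|---|---|---|
| 0.80 | 0.971 | 0.88 | 75% | 81% | 27% |
| 0.75 | 0.963 | 0.84 | 67% | 76% | 29% |
| 0.65 | 0.945 | 0.78 | 49% | 64% | 33% |
| 0.50 | 0.911 | 0.66 | 24% | 41% | 42% |

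**5. With a route term.** The slope is 1.000, the ratio 1.00, coverage 90%, and exp(route coefficient) returns F exactly. The 90% limits for F are a factor of exp(1.692 × √(0.0606/7.43)) = 1.17 either way at a CV of 25%. At a CV of 35% (σ² = 0.1156) the factor is 1.24.

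**6. Unequal cohorts.** The amendment (d) summary says Cohort 4 is to be repeated. If 300 mg SC had 12 active subjects (assumption), the weight would be 2.398/16.57 = 0.145 instead of 0.128. The ratio would be 100^(0.145 × ln 0.80) = 0.86 at F=0.80 and 100^(0.145 × ln 0.50) = 0.63 at F=0.50. The direction is the same and the bias slightly larger.

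**The case against.** **Pooling is inferred from silence.** The SAP never says the routes are combined, the code is labelled an example, and the table shells, which are not in these documents, may split by route. This does not cure the problem. Text and code agree on log-dose alone, nothing in either document separates the routes for this analysis, and a programmer following the SAP would fit one line.

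**The damage is limited.** This stands. Both extreme doses are IV, which damps the bias. Geometric means and CVs are planned for each dose level, so 10 and 1000 mg IV can be compared directly. PK is a secondary objective, the study is not powered for hypothesis tests, and escalation rests primarily on safety, with PK only supporting.

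**Stronger readings that the documents do not support.** A reader might infer that F cannot be estimated because no subject receives both routes. But the SAP formula never says it is applied per subject; applied to cohort geometric means it is an ordinary parallel-group estimate under linear PK. What is missing is the IV reference and a CI. A reader might also infer that the interval will miss 1 and the study will declare non-proportionality. At F of 0.75-0.80 the interval contains 1 in roughly 67-81% of trials at the two assumed CVs, and no acceptance limit is stated. Finally, Cmax is probably affected more, because slow SC absorption lowers the peak beyond the effect of F. The documents give no SC/IV Cmax ratio, so no figure can be attached.

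**Conclusion.** The point holds as a misspecified model. Fitted as written, on the protocol's own F of 80-50%, the expected 1000:10 mg AUC ratio is 0.88-0.66 when the truth is 1.00, and the model's between-subject variability is overstated. The direction of the bias is known in advance. Its size is modest at F of 0.75-0.80 and substantial towards 0.50.

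The ratios rest on exact within-route proportionality and equal cohorts; the coverage and CV figures also rest on the assumed CVs. The 0.75 value depends on the steady-state and single-dose AUCs being comparable. The primary safety objective and the sample size are unaffected. The correction is important but not must-fix.

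**What to change.** - **AUC:** add route (IV/SC) as a fixed effect to the power model in SAP 9.3.2 and its code. Report the slope, the 1000:10 mg ratio and the between-subject variability from that model.
- **Cmax:** assess proportionality within route, IV over 10-1000 mg and SC over 100-600 mg.
- **F:** report it at group level as exp(route coefficient) from the AUC(0-∞) model with its 90% CI, stating that this assumes a common slope for the two routes. This removes the need to choose an IV reference cohort for the SAP 9.3.1 formula.
- **Documentation:** record the change in SAP 11, which at present declares none.

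The cost is one model term and one residual degree of freedom (36 - 2 = 34 becomes 36 - 3 = 33). At an assumed CV of 30%, the median 90% CI for the ratio widens from 0.79-1.26 (pooled model with no true route effect) to 0.77-1.29. No new data, visits or subjects are needed.
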